### 13.3. Reporting of Serious Adverse Events

In the case of a serious adverse event, the investigator sends a report of the serious adverse events by e-mail or fax to the person in charge of Neurobiogen Clinical Development Headquarters within 24 hours of recognizing it, regardless of whether there is a causal relationship between the adverse event and the investigational drug.

|                              |                   |                          |                                                                           |
|------------------------------|-------------------|--------------------------|---------------------------------------------------------------------------|
| Neurobiogen Co., Ltd. | PV manager | [contact]  | E-mail: [contact] |
| C&R Research Inc. | PV manager | [contact] | E-mail: [contact]   |

Whenever possible, the initial report should include all items on the serious adverse event form, and the completed form should be sent to the sponsor. In addition to the serious adverse event form, the investigator should record the adverse event page of the case report form. If necessary, a follow-up report including all new information on the serious adverse event should be written in a serious adverse event form and sent to the sponsor, and should also be reported to the IRB according to the reporting procedure prescribed by the institution.

After receiving the initial report, the sponsor and the IRB should review the information and, if necessary, contact the investigator to obtain more detailed information. After reviewing the information of adverse event, the causal relationship with the investigational drug should be investigated.

If a suspected unexpected serious adverse reaction occurs, the sponsor should report it to the Minister of Food and Drug Safety within the following deadlines.

- Resulted in death or is life-threatening: Within 7 days from the date the sponsor was notified or became aware of the fact. In this case, the detailed information on the according adverse event must be submitted additionally within 8 days from the date of initial report.
- For all other suspected unexpected serious adverse reactions : Report within 15 days from the date the sponsor receives or becomes aware of the fact.

Although it does not correspond to a serious adverse event, the investigator is obliged to report in a special case (pregnancy). The sponsor is responsible for follow-up of pregnancy outcomes reported during the clinical study. If pregnancy occurs during the clinical study period (up to 30 days after the end of the clinical study) in the spouse (or partner) of the subject who administered the investigational drug, report it to the IRB and the sponsor within 24 hours of recognizing the pregnancy, and pregnancy processes and outcomes should be tracked and documented.

### 13.4. Adverse Events and Causal Relationship Evaluation with Investigational Drugs

#### 13.4.1. Severity

The severity of adverse events is classified according to NCI-CTCAE version 5.0 or higher, and adverse events not classified as NCI-CTCAE are evaluated according to the following five steps.

- Grade 1: Mild - Awareness of signs or symptoms, but easily tolerated
- Grade 2: Moderate - Discomfort severe enough to cause interference with usual activities
- Grade 3: Severe - Incapacitating and causing inability to perform normal activities
- Grade 4: Life-threatening consequences
- Grade 5: Death

#### 13.4.2. Actions Taken in relation to Adverse Events

- 1) Action taken with Investigational drug

- Drug-withdrawn
- Dose reduced
- Dose not changed
- Not applicable

2) Others

- Co-medication given
- Non-drug therapy given
- Not Done
- Unknown
- Not Applicable

#### 13.4.3. Outcome of Adverse Events

- Recovered
- Recovering
- Not recovered
- Recovered with sequelae
- Fatal
- Unknown

#### 13.4.4. Progress of Adverse Events

- Once
- Intermittent
- Continuous

#### 13.4.5. Causal Relationship with Investigational Drugs

Causal relationships with the investigational drugs are classified into the following six categories. And if necessary, the views of the principal investigator or investigator are recorded. Among the causal relationships, if it is evaluated “definitely related”, “probably related”, “possibly related”, and “unknown” except for “unlikely related” and “definitely not related”, it is evaluated as an adverse drug reaction that cannot exclude a causal relationship.

① Definitely related

- When there is evidence of drug administration and the temporal sequence of adverse events is appropriate
- The adverse event is most likely explained by the administration of the drug rather than any other reason.
- If the result is positive when re-administered (only if possible)

- When the adverse event is consistent with known information about the drug or drug in the same class
  - If there is a clinically reasonable response to discontinuation of administration
- ② Probably related
- When there is evidence of drug administration and the temporal sequence of adverse events is appropriate
  - The adverse event is most likely explained by the administration of the drug rather than any other reason.
  - If there is a clinically reasonable response to discontinuation of administration
  - If there is no re-administration information
- ③ Possibly related
- When there is evidence of drug administration and the temporal sequence of adverse events is appropriate
  - When the adverse event is judged to be attributable to the drug administration to the same extent as other probable causes.
  - In case of insufficient or unclear information regarding discontinuation of administration
- ④ Unlikely related
- When there is evidence of drug administration and the temporal sequence of the onset of adverse events is not appropriate
  - In the case of a temporary case that is unlikely to have a causal relationship with the administration of the drug
  - When there is a more probable cause for the adverse event
- ⑤ Definitely not related, None
- When the clinical study subject has not been administered the drug
  - When the temporal sequence between drug administration and the onset of the adverse event is not appropriate
  - When there is another apparent cause for the adverse event
- ⑥ Unknown, Unassessable
- When there is insufficient evidence to determine the relationship
  - In case the quality of the source data is low or there is inconsistency between the data
  - In case the information is insufficient or conflicting and cannot be determined, and it cannot be supplemented or verified.

### 13.5. Follow up of Adverse Events

Investigators should follow-up the subjects with adverse events until symptoms subside and abnormal clinical laboratory test results return to baseline, or until a satisfactory explanation for the observed changes is provided. If the subject does not make follow-up visits, check their health status in writing or by phone, etc., and record the reason why the follow-up visit is impossible as a source document.

When there is a change in status of the subject who has been previously reported a serious adverse event (eg, discharge after hospitalization, a worsening of the condition) or additional information is collected, the investigator delivers a serious adverse event report via fax or e-mail to the person in charge of Neurobiogen Clinical Development Headquarters within 24 hours of recognizing this.

## 14. Analytical and Statistical Considerations

### 14.1. Analysis Populations

1) Demographic information analysis group

Demographic information is analyzed for all subjects (Intention-To-Treat) assigned a randomization number.

2) Safety/tolerability evaluation population

All subjects who have been administered investigational drugs more than once. Analyze according to the type of dose group and treatment group.

3) Pharmacokinetic evaluation population

After completing the clinical study, the subjects who can evaluate the pharmacokinetic results are analyzed. Pharmacokinetic evaluation basically targets subjects with evaluable drug concentrations. If a subject drops out after receiving drug administration, the results obtained from the subject until the time of discontinuation or withdrawal may also be reviewed.

4) Pharmacodynamic evaluation population

After completing the clinical study, the subjects who can evaluate the pharmacodynamic results are analyzed.

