| Objectives                     | 
 
Primary objective: To evaluate the safety, tolerability and pharmacokinetics of a single and multiple oral dose of KDS2010 in healthy young and elderly subjects.
 
Secondary objective: To evaluate the pharmacodynamics of a single and multiple oral dose of KDS2010 in healthy young and elderly subjects.
 
                                                                                                                                                                                                                                                                                                                                                                                                                                                                                                                                                                                                                                                                                                                                                                                                                                                                                                                                                                                                                                                                                                                                                                                                                                                                                                                            |               |                            |                    |        |               |        |  |                    |   |       |            |                   |   |               |                           |   |   |       |            |                   |   |               |                           |   |    |                      |            |                   |   |               |                           |   |   |        |            |                    |   |               |                            |   |   |        |            |                    |   |

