| Cotinine & Urine drug screening       | ●          |                  |    |    |    |    |              |                  |
| Neurological examination  | ●          |                  | ●  |    |    | ●  | ●            | ●                |

 Randomization: On -1d, randomization is performed and a randomization number is assigned.

 Out-patient Visit: Subjects make outpatient visit to the Clinical Trials Center of Seoul National University Hospital on 5d, 6d, 7d, and post-study visit to perform the scheduled procedures.

 IP Administration: On 1d around 9am, the investigational drug is orally administered with 150mL of water on an empty stomach. Set the 1d administration time to 1d 0h and apply it to the subsequent study schedule.

 Vital signs: Blood pressure, heart rate, and body temperature are measured on screening, 1d pre-dose(0h), 1, 2, 4, 8, 12h post-dose, 2d 0h, 3d 0h, 4d 0h, 5d 0h, 6d 0h, 7d 0h and post-study visit.

 Physical examination: Physical examination is performed on Screening, 1d pre-dose(0h), 2d 0h, 3d 0h, 4d 0h, 5d 0h, 7d 0h and post-study visit.

 12-lead ECG: 12-lead ECG is measured on screening, 1d pre-dose(0h), 1, 2, 4, 8, 12h post-dose, 2d 0h, 3d 0h, 4d 0h, 5d 0h, 7d 0h and post-study visit.

 Pregnancy test: For all women of childbearing potential except surgical infertility, urine hCG test is performed, and it is measured before screening, -1d before randomization, and at PSV.

 Clinical laboratory test: Hematology, blood chemistry, coagulation and urinalysis are performed on screening, 1d pre-dose(0h), 2d 0h, 3d 0h, 4d 0h, 5d 0h, 7d 0h and post-study visit. Serology tests are performed only on screening.

 Neurological examination: Neurological examination is performed on screening, 1d pre-dose(0h), 4h, 12h post-dose, 4d 0h, 7d 0h and post-study visit. A full neurological examination is performed on screening, post-study visit, and a brief neurological examination is performed during other periods.

| 항목 | 일정                                              | Screening  | Treatment Period |    |    |    |    | Post Study Visit |           |
|----|-------------------------------------------------|------------|------------------|----|----|----|----|------------------|-----------|

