## 9. Study Subjects

### 9.1. Planned Subject Number and Rationale for sample size determination

This study is a phase 1 study to evaluate the safety, tolerability and pharmacokinetics of KDS2010 and to explore pharmacodynamics of KDS2010 after a single and multiple oral administration of KDS2010. Therefore, it is desirable to proceed with the minimum number of subjects within the limit that satisfies the purpose of the study, so this study is planned with a target number of up to 88 subjects, 8 in each cohort (including placebo).

If, according to the 9.3. Withdrawal Criteria, a subject drops out, and a replacement subject occurs according to the 9.4. Replacement of Study Subjects, the number of subjects may increase. (However, except for cases that only PSV visits are not conducted)

- **Single ascending dose study (including food effect study): Total 48 subjects**

| Cohort | Dosing groups | Dosage        |                           | Number of subjects |
|--------|---------------|---------------|---------------------------|--------------------|
| 1      | 30 mg         | Test group    | KDS2010 30 mg × 1         | 6                  |
|        |               | Control group | KDS2010 30 mg placebo × 1 | 2                  |
| 2      | 60 mg         | Test group    | KDS2010 30 mg × 2         | 6                  |

|                |                      |               |                            |   |
|----------------|----------------------|---------------|----------------------------|---|
|                |                      | Control group | KDS2010 30 mg placebo × 2  | 2 |
| 3 † | 120 mg (food effect) | Test group    | KDS2010 30 mg × 4          | 6 |
|                |                      | Control group | KDS2010 30 mg placebo × 4  | 2 |
| 4              | 240 mg               | Test group    | KDS2010 240 mg × 1         | 6 |
|                |                      | Control group | KDS2010 240 mg placebo × 1 | 2 |
| 5              | 480 mg               | Test group    | KDS2010 240 mg × 2         | 6 |
|                |                      | Control group | KDS2010 240 mg placebo × 2 | 2 |
| 6              | 960 mg               | Test group    | KDS2010 240 mg × 4         | 6 |
|                |                      | Control group | KDS2010 240 mg placebo × 4 | 2 |

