† For cohort 3, a fixed sequence, 2 period, cross over study will be conducted to evaluate the effect of food on the bioavailability of KDS2010. (If the dose escalation plan is changed, the dose for the evaluation of food effects may also be changed.)

• **Multiple ascending dose study††: Total 40 subjects**

| Cohort | Dosing groups    | Dosage        |                            | Number of subjects |
|--------|------------------|---------------|----------------------------|--------------------|
| 1      | 60 mg            | Test group    | KDS2010 30 mg × 2          | 6                  |
|        |                  | Control group | KDS2010 30 mg placebo × 2  | 2                  |
| 2      | 120 mg           | Test group    | KDS2010 30 mg × 4          | 6                  |
|        |                  | Control group | KDS2010 30 mg placebo × 4  | 2                  |
| 3      | 240 mg           | Test group    | KDS2010 240 mg × 1         | 6                  |
|        |                  | Control group | KDS2010 240 mg placebo × 1 | 2                  |
| 4      | 480 mg           | Test group    | KDS2010 240 mg × 2         | 6                  |
|        |                  | Control group | KDS2010 240 mg placebo × 2 | 2                  |
| 5      | 120 mg (elderly) | Test group    | KDS2010 30 mg × 4          | 6                  |
|        |                  | Control group | KDS2010 30 mg placebo × 4  | 2                  |

†† In the case of a multiple ascending dose study, subjects are administered once a day for 7 days.

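### Section 14.1 admits to the safety population only subjects dosed at least twice, which leaves out the 40 subjects planned to receive a single administration

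*Protocol*

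**What the plan says.** Section 14.1, item 2, sets the safety/tolerability population as "All subjects who have been administered investigational drugs more than once" and then asks for analysis by dose group and treatment group. No other section defines this population.

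The number of administrations per subject differs by part:

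- **Single ascending dose cohorts (30, 60, 240, 480 and 960 mg).** Footnote 3 of the flow chart reads "On 1d around 9am, the investigational drug is orally administered with 150mL of water on an empty stomach". The schedule marks no other dosing day, and section 10.1 agrees.
- **Cohort 3 (120 mg, food effect).** Section 9.1 says "For cohort 3, a fixed sequence, 2 period, cross over study will be conducted to evaluate the effect of food on the bioavailability of KDS2010", which gives one dose in each of two periods.
- **Multiple ascending dose cohorts.** Section 9.1 says "In the case of a multiple ascending dose study, subjects are administered once a day for 7 days".

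The primary objective in the synopsis is "To evaluate the safety, tolerability and pharmacokinetics of a single and multiple oral dose of KDS2010 in healthy young and elderly subjects".

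**The concern.** The threshold in section 14.1 is set one administration too high for a trial in which five of the eleven cohorts are dosed only once. Those five cohorts lie within the single-dose part, and single-dose safety is named in the primary objective. A programmer who follows section 14.1 as written would build a safety set without them. A programmer who tacitly reads the rule as one dose or more would depart from the protocol on a primary-objective analysis set.

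The same threshold acts on individuals in the repeat-dose parts. Anyone who stops after a first dose leaves the set, whatever the reason. Under section 9.4, a subject who drops out because of an adverse event after dosing is not replaced. Such a person, if dosed once, would be neither counted in the safety set nor replaced by someone who is. With six active subjects per cohort, one such loss is visible.

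**Working it through.** **Inputs.** Section 9.1 gives cohort sizes of 6 active and 2 placebo, with six single-dose cohorts ("Single ascending dose study (including food effect study): Total 48 subjects") and five multiple-dose cohorts ("Total 40 subjects"). Planned administrations per subject are 1 in single-dose cohorts 1, 2, 4, 5 and 6, 2 in cohort 3, and 7 in the multiple-dose part.

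**Step 1: reproduce the planned total.** 6 × (6 + 2) + 5 × (6 + 2) = 48 + 40 = 88, which matches section 9.1. Active: 11 × 6 = 66. Placebo: 11 × 2 = 22.

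**Step 2: apply the rule as written (two or more administrations).**

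| Group | Planned subjects | Administrations each | In the set as written | In the set if one dose suffices |
|---|---|---|---|---|
| Single dose: 30, 60, 240, 480, 960 mg | 5 × 8 = 40 | 1 | 0 | 40 |
| Single dose: 120 mg, food effect | 8 | 2 | 8 | 8 |
| Multiple dose, five cohorts | 5 × 8 = 40 | 7 | 40 | 40 |
| Total | 88 | | 48 | 88 |

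**Step 3: size of the loss.**

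- Excluded: 88 − 48 = 40, of whom 5 × 6 = 30 are active and 5 × 2 = 10 are placebo.
- Share of the trial: 40/88 = 45.5%.
- Share of the single-dose part: 40/48 = 83.3%.

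These counts assume that everyone receives all planned doses. Anyone in cohort 3 or the multiple-dose part who stops after one dose adds to the 40.

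**Step 4: dose levels left empty.** The 48 who remain received 120 mg (food effect) or 60, 120, 240 or 480 mg (multiple dose, with a further 120 mg cohort in the elderly). The 30 mg starting dose and the 960 mg top dose occur only in the excluded cohorts, so neither has anyone in the set. The single-dose groups at 60, 240 and 480 mg are also empty; those doses are represented only by repeat dosing.

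**Step 5: compare with the rest of the protocol.**

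- The primary objective covers safety after a single dose. The set in section 14.1 contains no subject from a cohort dosed only once.
- Section 13.1.1 defines an adverse event for any subject who has received the drug, with no minimum number of doses.
- Section 12.1.2 asks for adverse event counts and rates by dose group and treatment group. Five of the six single-dose groups would have a denominator of zero.
- Sections 10.5 and 10.6 base the escalation and stopping review on everyone dosed.

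All four imply a one-dose threshold. Only section 14.1 implies two.

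**The case against.** The strongest reply is that this is a slip for a one-dose threshold and that no analyst would apply it literally. The primary objective, the adverse event definition, the tabulation by dose group and the escalation scope all show the intent, and sections 9.3 and 10.7.3 have subjects who drop out after dosing assessed for safety. As an account of intent this is probably right. It does not repair the text: those sections show that the sentence is wrong, but none replaces it as the definition of the analysis set. Nor is this a detail left to a statistical analysis plan. The protocol fixes the rule, so a plan with the correct rule would contradict it.

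Four stronger readings might be inferred, and the documents do not support them:

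- **That the whole single-dose part is lost.** The 8 food-effect subjects belong to that part but are dosed twice, so they stay in if they receive both doses. The loss is 40 of 48.
- **That 30 mg and 960 mg would have no safety data.** Adverse events, vital signs, ECGs, laboratory tests and neurological examinations are scheduled for every single-dose cohort. What would be missing is their place in the analysis set.
- **That dose escalation is compromised.** Sections 10.5 and 10.6 use their own scope, which is every dosed subject.
- **That the rule biases the result in favour of the drug.** Excluding people who stop after one dose could hide early adverse events. However, section 9.3 also lists reasons for dropout unrelated to safety, the rule applies equally to active and placebo, no dropout rate is given, and the safety analysis is descriptive. Neither the direction nor the size of a bias can be derived.

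**Conclusion.** The definition is wrong as written and should be corrected before the safety analysis set is built. Applied literally, and with all planned doses given, it keeps 48 of 88 subjects and omits 40 (45.5%; 30 active, 10 placebo), leaving the lowest and highest dose levels unrepresented. The conclusion rests on the ordinary meaning of the phrase and on the dosing schedules; it needs no assumption about effect, variability or dropout. The effect is confined to the reported safety analysis set. Data collection and escalation decisions do not depend on this sentence.

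**What to change.** In section 14.1, item 2, change *more than once* to *at least once*, and apply the definition to all three parts: single ascending dose, food effect and multiple ascending dose. Keep the following sentence on analysis by dose group and treatment group. All 88 planned subjects (66 active, 22 placebo) then enter the safety population once dosed, and anyone who stops after one administration is counted.

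The cost is one phrase, handled as a wording amendment under section 17.6. Visits, samples, subject numbers and conduct do not change. Any statistical analysis plan should carry the same definition.
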